#### Ethical considerations

This study protocol and its procedures have been approved by the University of Miami Miller School of Medicine’s Institutional Review Board (study # 20220518). The protocol is in full compliance with the standards set forth by the UM Miller School of Medicine IRB. During the informed consent process, expectant and postpartum moms will be informed on the potential risks and benefits of the research study and have the opportunity to ask the research staff clarifying questions.

### Data collection

#### Baseline and follow-up

After being screened and providing consent for the study, participants will receive an email with a link to complete the baseline survey online via REDCap. This survey includes questionnaires and well-validated scales that collect data on demographics, health history, stress levels, experiences of discrimination, sleep quality, emotional support, and overall pregnancy experience (see **Table 2**). Study team members may help the participant complete the baseline survey over the phone, on Zoom, or in person if necessary.

**Table 2 T2:** Study measures.

Variable*	Baseline	3 months	1 year
Tracking Form and Demographic Questionnaire	x		
Pregnancy Health History or Prenatal Screening Questionnaire (28)	x		
Perceived Stress Scale (29)	x	x	x
Everyday Discrimination Scale (Short Form) (30, 31)	x		
PROMIS^®^ Item Bank v1.0–Sleep Disturbance–Short Form 4a (32)	x	x	x
PROMIS^®^ Item Bank v2.0–Emotional Support–Short Form 4a (33)	x	x	x
Maternal Self-Efficacy Questionnaire (34)	x	x	x
Pregnancy Experience Scale (PES) (35)	x		
Childbirth Experience Questionnaire (CEQ) (36)	x		
Edinburgh Postnatal Depression Scale (EPDS) (37)	x		
User Experience Questionnaire (38)	x		
Virtual Reality Neuroscience Questionnaire (VRNQ) (39)	x		

*Some of these questionnaires have questions about the father. As the father is not relevant and is not a secondary participant in this study, these questions referring to the father have been removed.

Participants will be invited to complete the same survey three months following the completion of the intervention and will be monitored for 1 year. There will also be an optional 1-year follow-up (See **Figure 3**).

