### Study procedures

#### Timeline

The Nurturing Moms study will assess the effectiveness of NurtureVR, a digital solution for maternal mental health, across four phases. In phase I, participants will be recruited from health clinics, community-based organizations, and online platforms. Interested individuals will receive a screening form link via REDCap to determine eligibility based on inclusion and exclusion criteria (described below). Eligible participants will be contacted by a study team member to review and electronically sign an informed consent form before completing a 10–20-minute baseline questionnaire on the same platform.

In Phase II, VR headsets will be shipped to participants one week after the baseline questionnaire is completed. Participants will use the NurtureVR for five weeks and will be asked to rate their level of stress, anxiety, mood, and pain level after each VR session using well-validated scales. In Phase III, participants will repeat the surveys three months after completion of the digital intervention. Additionally, two focus group sessions will be held with five participants each, focusing on Black and Latina expectant and postpartum women’s views on resilience, their NurtureVR experiences, perceptions, and recommendations for using VR for stress management. Each focus group will be conducted online to ensure accessibility, with one session scheduled before and one after the participants’ completion of the NurtureVR program. Discussions will follow a semi-structured format, encouraging open dialogue around key themes such as resilience and VR experience. For data analysis, we will employ thematic analysis, using NVivo software to organize and code responses. This approach allows for consistent identification of recurring themes, patterns, and variations in participants’ feedback, facilitating a thorough understanding of their experiences and recommendations. Coding will be iterative and conducted by multiple researchers to enhance reliability and capture diverse perspectives.

The final phase, which is optional, invites participants to repeat the surveys one year after completing NurtureVR. This comprehensive approach aims to provide a thorough evaluation of NurtureVR’s impact on maternal mental health in the short and longer term (See **Figure 1**).

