### Study instruments

Tracking Form and Demographic Questionnaire: This form consists of two questionnaires to collect demographic information including age, race, and sex. The forms also capture socio-economic information such as employment, education, income, zip code, and other geographical data.Pregnancy Health History or Prenatal Screening Questionnaire: This 3-page questionnaire developed by the American Medical Association can provide useful material to researchers and physicians who want to gather information either prior to pregnancy or during a pregnancy. This form can help determine the risk of a baby having chromosomal conditions or neural tube defects based on the parents’ family history. The form captures past medical history of the father and mother, mother’s history of pregnancies, and exposures during pregnancy (28).Perceived Stress Scale: The perceived stress scale developed in 1983 is a 10-item questionnaire used to gauge stress levels in individuals aged 12 and older. It examines the degree to which situations are perceived as stressful in terms of how unpredictable, uncontrollable, and overloaded respondents find their lives. Score ranges from 0 to 40, with higher scores representing higher levels of stress. Average scores are calculated by adding up the scores and dividing by the number of items, providing a useful indicator for evaluating the overall level of agreement on the likert scale (where 0 = Never, 1 = Almost never, 2 = Sometimes, 3 = Fairly often, and 4 = Very Often) The perceived stress scale has been shown to have a coefficient alpha reliability of.84,.84, and.86 in three studied samples with a test-retest correlation of.85 (29).Everyday Discrimination Scale (Short Form): The everyday discrimination is a five-item instrument measuring experiences of daily discrimination followed by a question about what the person believes was the reason for that daily discrimination. Responses are coded on a 6-point Likert scale ranging from ‘never ‘= 1 to ‘almost everyday’ = 6. Responses are summed across items to produce a score ranging from 10 to 60 (40). The everyday discrimination scale, developed by David Williams in 1997, has shown high levels of internal consistency, convergent validity and divergent validity among African American men and women, and has been widely used in studies of discrimination and health (30, 31).PROMIS^®^ Item Bank v1.0–Sleep Disturbance–Short Form 4a: The PROMIS Sleep Disturbance and Sleep-Related Impairment item banks were developed using a rigorous and systematic methodology, including literature reviews, qualitative item review, focus groups, cognitive interviewing, and psychometric testing. The short form was developed from the full 27-item bank and has been shown to have convergent validity, construct validity, and reliability similar to the full bank. The short form is an 8-item form measuring the quality of sleep and sleep disturbance over the past 7 days. Four items use an intensity scale (not at all, a little bit, somewhat, quite a bit, very much), three items use a frequency scale (never, rarely, sometimes, often, always), and one item (S109) assessing overall sleep quality uses a scale of very poor, poor, fair, good, very good (32).PROMIS^®^ Item Bank v2.0–Emotional Support–Short Form 4a: The PROMIS Emotional Support Short Form was developed by domain experts from the full bank to capture the range of traits and allow researchers to study secondary outcomes without full additional measures. It consists of 4 statements assessing perceived feelings of being cared for and valued as a person. Responses are coded on a 5-point Likert scale ranging from 1 = never to 5 = always. The convergent validity has been supported by strong correlations between the PROMIS Emotional Support short form and measures of similar constructs. Discriminant validity has also been confirmed by negligible correlations between the emotional support measure and measures of dissimilar constructs (33).Maternal Self-Efficacy Questionnaire: The Maternal Self-Efficacy Questionnaire consists of 10 statements assessing mothers’ confidence in their ability to perform parenting-specific tasks such as understanding the baby’s needs and feelings, talking, reading to and playing with the baby, and taking the baby for regular clinic/doctor check-ups. Responses are coded on a 4-point Likert scale (1 = much worse, 2 = somewhat worse, 3 = as good, 4 = better than others). The questionnaire has been found reliable, face and content validity have been shown to be adequate as well as internal consistency and test–retest reliability for the assessment of maternal self-efficacy (34).Pregnancy Experience Scale (PES): The pregnancy experience scale consists of 10 statements measuring how much different aspects of pregnancy have made the mother feel either uplifted and happy or upset and negative. Each response is rated from 0 = not at all to 3 = a great deal. Internal reliability, test-retest reliability, and convergent validity were comparable to the original 41-item PES developed in 2004 (35).Childbirth Experience Questionnaire (CEQ): The childbirth experience questionnaire consists of 22 statements assessing four domains of the childbirth experience; Own capacity, Professional support, Participation, and Perceived safety. It evaluates women’s experience of labor and childbirth, including their perceptions and feelings. For 19 of the items the response format is a 4-point Likert Scale whereas the last three items use a visual analogue scale (VAS). The scoring range is 1 to 4 where higher ratings reflect more positive experiences. The CEQ has demonstrated internal consistency, discriminant validity, equal item-hypothesized scale correlation, and item equal variance (36).Edinburgh Postnatal Depression Scale (EPDS): The Edinburgh Postnatal Depression Scale developed in 1987 remains a prominent tool for measuring postpartum depression. It consists of 10 statements which identify signs and symptoms of depression in the postnatal period. Responses are scored 0, 1, 2, or 3 according to increased severity of the symptom. Items marked with an asterisk (*) are reverse scored (i.e., 3, 2, 1, and 0). The total score is determined by adding together the scores for each of the 10 items. The EPDS demonstrates acceptable sensitivity, specificity and positive predictive value. It has been used in many studies, and has been introduced as a valuable and powerful postnatal depression screening tool in different cultures (37).User Experience Questionnaire: The User Experience Questionnaire consists of 26-items measuring whether people find the using the NurtureVR product to be an overall positive or negative experience. A seven stage scale is used between two opposing descriptors of the user experience. Mothers rate more closely to the descriptor they identify with (38).Virtual Reality Neuroscience Questionnaire (VRNQ): The Virtual Reality Neuroscience Questionnaire consists of 20-item questionnaire measuring the quality of user experience, game mechanics, and in-game assistance, as well as the intensity of the VR induced symptoms and effects. Responses are coded on a 7-point Likert scale, ranging from 1 = extremely low to 7 = extremely high. The higher scores indicate a more positive outcome (39).

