## Conclusion

In conclusion, the *Nurturing Moms* protocol aims to investigate the potential efficacy of NurtureVR, a virtual reality based maternal health and wellness program, in reducing stress among expectant and postpartum Black and Latina women. The disproportionate rates of psychological symptoms among this population, heightened by factors like economic hardships and limited access to psychoeducation, highlight the critical need for customized digital interventions. The present study aims to evaluate the effects of the NurtureVR program not only on maternal stress but also on improving sleep quality and enhancing health literacy during and after pregnancy. Our efforts to maximize the advantages of innovative digital solutions like NurtureVR, which incorporates mindfulness techniques, relaxation, and virtual reality-enabled guided imagery, aligns with recent evidence supporting the effectiveness of psychoeducation and early intervention in improving adverse mental health outcomes among expectant and postpartum women.

The pre-and post-study design provides participants with a holistic approach spanning pregnancy, labor and delivery, and postpartum phases. Implementing comprehensive learning modules, stress-coping mechanisms, and family involvement helps uplift mothers and nurtures the mental well-being of both mother and baby. The Nurturing Moms study not only spotlights the significance of interventions targeting maternal stress among minority populations but also contributes to the growing field of perinatal mental health by leveraging advanced digital solutions to support expectant and postpartum mothers.

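### Table 2 schedules every pregnancy- or birth-related instrument at baseline only, against the text, so women enrolled while pregnant have no usable measure of the index birth

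*Protocol article*

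**What the plan says.** Table 2 (Data collection, Baseline and follow-up) is a row-by-row schedule with columns for baseline, 3 months and 1 year. Three rows concern pregnancy or birth: "Pregnancy Health History or Prenatal Screening Questionnaire (28", the Pregnancy Experience Scale, and "Childbirth Experience Questionnaire (CEQ) (36". Each is marked at baseline only, as is "Tracking Form and Demographic Questionnaire". Only the Perceived Stress Scale, the two PROMIS short forms (sleep disturbance, emotional support) and the Maternal Self-Efficacy Questionnaire are marked at all three times.

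The text differs. Under Timeline, "participants will repeat the surveys three months after completion of the digital intervention", and the sentence below Table 2 likewise has participants complete the baseline survey again at that point.

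Under Study instruments, the tracking form is demographic: "This form consists of two questionnaires to collect demographic information including age, race, and sex". The health-history form serves to "gather information either prior to pregnancy or during a pregnancy". The CEQ is the one instrument directed at the birth: "It evaluates women’s experience of labor and childbirth, including their perceptions and feelings".

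Study design overview makes improvement in childbirth experience part of the second objective. The Statistical analysis plan section names the CEQ as a postpartum factor in the regression of mental health and sleep outcomes. The Conclusion describes the design as "a holistic approach spanning pregnancy, labor and delivery, and postpartum phases".

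**The concern.** An expectant woman cannot answer the CEQ about the index birth at baseline. If she has given birth before, her baseline answers can only concern an earlier birth. On the table's schedule she is never asked again. For women enrolled postpartum, the birth precedes the programme. It is therefore the expectant women who can show whether the programme improves the childbirth experience, and they are the ones without a usable measurement. The planned regression factor has the same gap in this group.

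Timing is also at stake. For many expectant women the birth falls between the pre and post surveys. Stress and sleep at the post survey plausibly depend on the birth and on the time since it, and none of the described instruments supplies a birth date. Without one, weeks since birth at each survey cannot be derived, and some programme sessions cannot be reliably classed as before, during or after birth.

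**Working it through.** The article gives no figure of its own for the survey interval or for the number of births within it, so there is none to reproduce. The inputs below come from its text, and assumptions are marked.

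**1. Interval between surveys.** Timeline: headset shipped 1 week after baseline, 5 weeks of use, repeat survey 3 months after completion. Taking 3 months as 13 weeks: 1 + 5 + 13 = 19 weeks.

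**2. Who delivers between the surveys.** Participants: pregnant women enter at under 36 weeks, with no lower limit. Assuming birth at 40 weeks, the entry threshold is 40 − 19 = 21 weeks. It is 37 − 19 = 18 weeks for birth at 37, and 42 − 19 = 23 weeks for birth at 42. Women entering from about 21 to under 36 weeks usually deliver between the two surveys, and earlier entrants are usually still pregnant at the second.

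**3. Share of the expectant group.** The distribution of gestation at entry is not given, so uniform entry is assumed.
- From 0 to 36 weeks: (36 − 21)/36 = 15/36 = 0.417, or 0.417 × 25 ≈ 10 of 25 women.
- From 12 to 36 weeks: (36 − 21)/(36 − 12) = 15/24 = 0.625, or 0.625 × 25 ≈ 16 of 25 women.

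**4. Placing exposure relative to birth.** On the Timeline account, use ends about 1 + 5 = 6 weeks after baseline (delivery time and delays ignored). With birth at 40 weeks, a woman entering before 40 − 6 = 34 weeks finishes before birth. The limit is 37 − 6 = 31 weeks for birth at 37, and 42 − 6 = 36 weeks for birth at 42. On this account, real ambiguity is confined to entry from about 31 to under 36 weeks. With birth at 40 weeks and the 12-to-36-week assumption, women straddling the birth are 2/24 = 0.083, about 2 of 25.

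Other sections give different accounts. The Abstract places use in the third trimester and six weeks postpartum, with follow-up at six weeks postpartum. The NurtureVR section has five weeks prenatal, optional use in labor and five weeks postpartum. On those accounts exposure spans the birth for expectant women generally, and a follow-up counted from the birth needs a birth date to be scheduled.

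**5. Table against text.** If the table governs, nothing at follow-up concerns the birth. If the text governs, the health-history form and the CEQ are repeated. The CEQ would then be answered after birth by women who have delivered. The health-history form includes the mother's history of pregnancies and might pick up part of the birth. Even so, no instrument is described as recording the date of birth, gestation at birth, mode of delivery or neonatal admission.

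**The case against.** The strongest reply is that this is a condensed article. Delivery date, mode of delivery and neonatal admission are case-report-form items, and a table of study measures is not a data dictionary. The Data and safety monitoring plan also commits to assessing and reporting adverse events, a plausible route by which a loss or serious complication would become known. This stands: the article does not show that the study will be ignorant of the birth, and a reader should not infer that. It does not answer the CEQ row, where the table is explicit and conflicts with the text.

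Second, the table's columns may simply be misprinted. The User Experience Questionnaire and the Virtual Reality Neuroscience Questionnaire are also marked at baseline only, although headsets ship a week later. That is a fair reason to call this a contradiction to be reconciled, not a settled omission.

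Third, one might infer that exposure cannot be placed relative to birth at all. The documents do not support that. The Administrative Control Panel time-stamps module use (VR modules), gestation is screened at entry, Table 1 groups modules by period, and on the Timeline account few women straddle the birth. What remains is that module labels show content and not whether the woman had delivered, that projection from entry gestation fails for preterm birth, and that the other accounts of the programme span the birth.

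Fourth, repeating the tracking and health-history forms would not clearly solve the problem, given how they are described. That is right, and it is why the CEQ row carries the point.

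Finally, the attribution problem belongs to any design without controls, and the Discussion already concedes it. Birth data allow description and sensitivity analysis, no more.

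**Conclusion.** The point holds in this form: Table 2 and the text disagree about what is repeated, and on the table's schedule the index birth of women enrolled while pregnant has no usable measure, despite a secondary objective and a planned regression factor that depend on one. None of the described instruments supplies a birth date.

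On the 19-week interval, about 42% to 62% of expectant women deliver between the surveys. This rests on birth at 40 weeks and on uniform entry from 0 or from 12 weeks to 36 weeks; neither assumption is given by the article.

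A reader might infer that all 25 expectant women are affected. That combines the Abstract's third-trimester use with the later survey timing in Timeline, and the entry criteria set no lower gestational limit. Nor can a bias in the stress result be sized: that would need an assumed number of complicated births and an assumed effect on stress, and the documents give neither.

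**What to change.** 1. Reconcile Table 2 with the statements in Timeline and below the table on what is repeated. Reconcile also the differing accounts of programme and follow-up timing in the Abstract, Timeline and NurtureVR sections.
2. Schedule the CEQ after birth for women enrolled while pregnant.
3. Unless the full case report forms already hold them, add four items to the follow-up REDCap survey: date and outcome of the end of pregnancy, gestation at birth, mode of delivery, and neonatal admission.
4. Use these to derive weeks since birth at each survey, to class control-panel sessions as before, during or after birth, and to report the expectant group's stress and sleep change descriptively with and without complicated births.
5. State that this does not remove the confounding of programme with birth in a design without controls.

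The four items cost a minor amendment and about one minute per woman, with a small added reporting burden for women who had a poor outcome. The 22-item CEQ adds a further questionnaire after birth, unless the full survey is already meant to be repeated.

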Unlike prior studies using VR as a reaction to treat health disturbances, the protocol described in this manuscript, *Nurturing Moms*, is designed as a *preventative* measure for Latina and African-American mothers. NurtureVR, a digital maternal mental health program, developed by BehaVR, was designed to: a) guide mothers through pregnancy via education and empathy and b) help them identify and address potential mental health concerns before these become major barriers to maternal and infant health and well-being. There is minimal research using therapeutic VR for maternal mental health in a diverse group of expecting mothers. Such work is timely, as the scientific community has only recently begun to address the importance of including diverse populations in research (25, 26). This is particularly applicable to digital health research, as the United States healthcare system continues to rapidly integrate technology into patient care. Considering this, researchers and clinicians must make a conscious effort to ensure digital health tools are accessible to all populations, especially those who have been historically neglected by the healthcare system (27).

*The Nurturing Moms* protocol (NurtureVR) addresses the aforementioned gaps in the literature by exploring Latina and Black perinatal mental health and related factors. Our primary objective is to assess whether NurtureVR reduces stress levels and mental health symptoms of pregnant and postpartum Black and Latina women. Our secondary objective is to assess whether NurtureVR improves sleep, as well as pregnancy and childbirth experiences. Our tertiary objective is to examine whether NurtureVR improves pregnancy/postpartum health literacy. We hypothesize that NurtureVR’s combination of mindfulness, relaxation, and education will be protective against postpartum depression, beneficial for pregnancy and birth experiences, and increase health literacy.

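### Table 2 schedules the depression, pregnancy-experience, childbirth-experience and VR-usability scales at baseline only, against the follow-up text and the objectives; childbirth experience has no pre-post comparison on either reading

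*Protocol article*

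**What the plan says.** Table 2 (Data collection, Baseline and follow-up) has 12 rows and columns for baseline, 3 months and 1 year. Four rows are marked in all three columns: "Perceived Stress Scale (29)", PROMIS Sleep Disturbance, PROMIS Emotional Support and Maternal Self-Efficacy. The rows "Edinburgh Postnatal Depression Scale (EPDS) (37)", "Pregnancy Experience Scale (PES) (35)" and "Childbirth Experience Questionnaire (CEQ) (36)" carry one mark each, under baseline. The User Experience Questionnaire and the VRNQ are marked the same way.

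The text describes a full repeat. Below the table: "Participants will be invited to complete the same survey three months following the completion of the intervention". Under Timeline: "In Phase III, participants will repeat the surveys three months after completion of the digital intervention", with an optional repeat at one year. The Abstract instead places follow-up at six weeks postpartum.

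The primary objective (Introduction and Study design overview) covers mental health symptoms as well as stress. The next is: "Our secondary objective is to assess whether NurtureVR improves sleep, as well as pregnancy and childbirth experiences". The hypothesis is that NurtureVR "will be protective against postpartum depression, beneficial for pregnancy and birth experiences, and increase health literacy". The Statistical analysis plan section counts mental health scores among the main dependent measures and uses the User Experience Questionnaire and VRNQ to judge feasibility, usability and acceptability.

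**The concern.** A single-group pre-post study estimates an effect only where a scale has a value before and a value after exposure. As printed, Table 2 gives no after-value for the scales that carry depression, pregnancy experience and childbirth experience, and none for the two questionnaires about using the product. Staff who build the REDCap surveys from the table would collect different data from staff who follow the text. A depression score not collected at follow-up cannot be recovered later.

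Separately, CEQ and PES refer to events (a birth, a current pregnancy) that do not line up with the before and after time points in either cohort. Simply adding marks to the table would not make those objectives testable.

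**Working it through.** **1. Count in Table 2.** Rows: 12. Marked after baseline: 4. Baseline only: 12 − 4 = 8. Three of the eight (demographics, health history, everyday discrimination) are background descriptors, for which one value is enough. The other 8 − 3 = 5 are EPDS, PES, CEQ, the User Experience Questionnaire and the VRNQ. Each has one planned assessment and none after baseline, so under the table the number of women with a change score on any of them is 0 of 50.

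**2. Objectives against the two readings.**

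| Construct | If Table 2 governs | If the text governs |
|---|---|---|
| Perceived stress | repeated | repeated |
| Sleep | repeated | repeated |
| Anxiety, mood | brief ratings around VR sessions | same |
| Depression (EPDS) | no follow-up value | repeated at 3 months |
| Pregnancy experience (PES) | no follow-up value | repeated, but see step 4 |
| Childbirth experience (CEQ) | no follow-up value | repeated, but see step 3 |

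**3. CEQ by cohort.**
- Expectant (planned n = 25): no index birth to rate at baseline. A later CEQ gives a post-only value. An earlier child's birth would be a different birth.
- Postpartum (planned n = 25): the birth preceded the intervention. A second CEQ rates the same unexposed birth again.

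Women with a before-and-after CEQ for a birth that followed exposure: 0 + 0 = 0 of 50, on either reading.

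**4. PES timing.** From the Timeline: 1 week to shipping + 5 weeks of use + 3 months (about 13 weeks) = about 19 weeks after baseline, counting use from shipment. Gestational age at delivery is an assumption. With delivery at 40 weeks, a woman is still pregnant at follow-up only if enrolled before 40 − 19 = 21 weeks; with delivery at 37 to 42 weeks, before 18 to 23 weeks. Eligibility runs to 36 weeks. If use falls in the third trimester, as the Abstract says, and that is taken to begin at 28 weeks (assumption), the earliest follow-up is at 28 + 5 + 13 = 46 weeks, so nobody would still be pregnant. Women enrolled postpartum are not pregnant with the index child at either time.

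The end of the programme is 1 + 5 = 6 weeks after baseline. Women enrolled before 40 − 6 = 34 weeks (31 to 36 for delivery at 37 to 42) would then still be pregnant.

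**5. Usability questionnaires.** Headsets ship one week after the baseline questionnaire. Apart from a possible demonstration at a recruitment table, a baseline User Experience Questionnaire or VRNQ rates a product the woman has not used.

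**6. The plan's own sample-size figure.** The Discussion gives a one-sample t-test with effect size 0.5, power 95% and alpha 0.05, hence N = 45 and df = 44. This reproduces one-sided: noncentrality 0.5 × √45 = 3.35, power 0.951. (Two-sided, N would be 54.) In a pre-post study that test needs one change score per woman, so under Table 2 the Discussion's statement about power for mental health symptoms cannot extend to EPDS.

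**The case against.** The best answer is that Table 2 is simply misprinted. Two separate passages say the surveys are repeated, and the usability entries cannot be right as they stand, so the lower block of the table is doubtful as a whole. The timeline figure, which might settle it, is not shown. This stands: the firm finding is a contradiction between table and text, and the loss of EPDS follow-up is conditional on the table.

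A reader might go further and infer that the mental-health part of the primary objective is wholly untestable. The document does not support that. Perceived stress is repeated on both readings, and the analysis of the primary objective is framed around stress over time. Anxiety and mood are rated around VR sessions (Weekly mood state surveys). Those are brief momentary ratings and do not replace a depression scale at follow-up, but symptom data after baseline do exist. Sleep, part of the secondary objective, is also repeated.

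A reader might also infer that the multiple-imputation rule would fill in childbirth scores for women who have not given birth. The article does not say so. It lists CEQ as a postpartum factor, and a questionnaire that does not apply is not ordinarily treated as missing. Such detail may lie in a fuller plan.

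Baseline values also have stated uses: CEQ as an explanatory variable and baseline mental health as a covariate. That is fair, but it does not meet the stated objectives. Finally, the Discussion calls feasibility and acceptability the primary aim. That does not help the table, because the two questionnaires assigned to that aim are marked before the headset ships.

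**Conclusion.** Table 2 contradicts the follow-up text and does not fit the stated objectives. This must be put right before the surveys are built.

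- **Conditional on Table 2:** 0 of 50 women have a post-intervention EPDS, so change in depressive symptoms and the postpartum-depression hypothesis cannot be tested. If the text governs, EPDS is available at three months.
- **On either reading:** 0 of 50 have a pre-post CEQ for a birth after exposure. At most the 25 expectant women can give a post-only value.
- **On either reading:** PES at the three-month follow-up comes after delivery for most or all expectant women. This rests on follow-up about 19 weeks after baseline and delivery at 37 to 42 weeks. It would not hold for women enrolled before roughly 18 to 23 weeks.
- **As printed:** the User Experience Questionnaire and VRNQ are scheduled before the product is used.

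**What to change.** Reconcile Table 2 with the Abstract, the Timeline and the sentence below the table, showing time points by cohort.

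- **EPDS:** mark it at the 3-month and 1-year follow-ups. If baseline only is intended, remove depression from the objectives and hypothesis.
- **CEQ:** give it after the index birth in the expectant cohort and treat it as a baseline descriptor in the postpartum cohort. Limit the childbirth-experience objective to women who deliver after exposure, as a descriptive post-only result.
- **PES:** give it at the end of the five-week programme to women still pregnant, or drop the objective on change in pregnancy experience.
- **User Experience Questionnaire and VRNQ:** move both to after VR use.

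The cost is a table edit, cohort branching in REDCap and a slightly longer online follow-up survey (EPDS has 10 items, CEQ 22). Keeping PES adds a short survey at the end of the programme. The stated objectives become narrower, and the childbirth result rests on no more than the 25 expectant women, without a before-value.
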